### Statistical analysis

The primary study hypothesis is that intratympanic methylprednisolone is superior to systemic methylprednisolone for the treatment of hearing loss. Based on a previous study [12], we will define intratympanic treatment as superior if the mean post-treatment change in dB PTA in the systemic group exceeds that in the intratympanic group. The primary outcome, i.e., change in PTA, will be calculated as the difference between the baseline and 30-day follow-up visit. This will then be compared between the two groups using a one-sided *t* test. The two groups will be compared using the 95% confidence interval method to determine superiority.

Data will be statistically analyzed using PASW Statistics 18.0 (IBM SPSS Inc., Armonk, New York, USA) and SAS 9.2 software (SAS Institute Inc., Cary, USA). For secondary outcomes, a two-tailed *P* value < 0.05 will be considered statistically significant. The analysis will be based on the thematic intention-to-treat principles.

We will evaluate safety by tabulating AEs using descriptive statistics at baseline and follow-up visits for each group. Fisher’s exact test and the chi-square test will be used to compare categorical variables between the two groups.

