### Outcome measures

The primary outcome measure will be the change in PTA (dB) from the first audiogram to the 30-day follow-up audiogram. Hearing will be evaluated using air-conducted and bone-conducted PTA after 1 and 14 days of treatment, and at 30 and 90 days of follow up.

Secondary outcome measures will include PTA at 90 days, visual analog tinnitus scale, visual analog vertigo scale, visual analog aural fullness scale, fasting blood glucose and 2-h postprandial blood glucose during treatment, and the change in glycosylated hemoglobin (HbA1C) levels. Vital signs and otological physical examination will be performed at each follow-up visit (Fig. 2).

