### Sample size calculation

The purpose of the proposed study is to compare the effectiveness of PTA by one-sided *t* test, which is used with the 95% confidence interval method. The difference in PTA is reported in previous publications as 30.7 in the experimental group and as 28.7 in the control group. The difference in the mean was 2, and the combined standard deviation was 3. The type 1 error was 2.5% and statistical power was 90%. Considering a 5% loss rate, 96 samples are required. This allows for 48 participants in the study group and 48 in the control group.

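### The one-sided superiority rule depends on a sign for change in PTA that is never defined, and on the improvement scale used for every change figure in the article it is reversed

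*Protocol article*

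**What the plan says.** The Statistical analysis section opens with the aim: "The primary study hypothesis is that intratympanic methylprednisolone is superior to systemic methylprednisolone for the treatment of hearing loss". It then gives the decision rule, under which intratympanic treatment is "superior if the mean post-treatment change in dB PTA in the systemic group exceeds that in the intratympanic group". The variable is described without a sign: "change in PTA, will be calculated as the difference between the baseline and 30-day follow-up visit". The same paragraph specifies a one-sided t test and a 95% confidence interval method for judging superiority.

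The Outcome measures section words the endpoint this way: "The primary outcome measure will be the change in PTA (dB) from the first audiogram to the 30-day follow-up audiogram". The Abstract uses the same from-first-to-30-day form.

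The Sample size calculation section gives positive values, with the larger one in the experimental arm: "The difference in PTA is reported in previous publications as 30.7 in the experimental group and as 28.7 in the control group". It continues: "The difference in the mean was 2, and the combined standard deviation was 3". The type 1 error is 2.5% and the power 90%.

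The Discussion gives PTA changes twice, each time as positive improvement. For the cited multicentre trial it reports 30.7 dB with oral prednisone and 28.7 dB with intratympanic treatment. For the trial's own pilot it reports 40 dB intratympanic and 30 dB systemic.

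**The concern.** PTA is a threshold, so a lower value means better hearing. A change in PTA can therefore be written in two ways: as improvement (baseline minus day 30, larger is better) or as raw change (day 30 minus baseline, more negative is better). Which arm should have the larger mean depends entirely on that choice.

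The primary test is one-sided, so its direction is part of the hypothesis. The article prints a direction but not the sign convention that would give it meaning, and its own change figures follow the convention under which the printed direction is wrong. An analyst who computes improvement, as the article does throughout, and then applies the rule literally would be testing for a systemic advantage and labelling it intratympanic superiority.

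**Working it through.** **Inputs.** Difference 2 dB, SD 3 dB, one-sided alpha 0.025, power 90%, 48 per arm (all from Sample size calculation); one-sided t test (Statistical analysis).

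**Step 1: the plan's own figure.** Normal approximation, per arm:

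n = 2 × (z₀.₉₇₅ + z₀.₉₀)² × (SD/difference)² = 2 × (1.960 + 1.282)² × (3/2)² ≈ 47.3, rounded up to 48, or 96 in total.

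This matches the stated 96 before any allowance for loss. With the stated 5% loss it would be 48/0.95 = 50.5, so 51 per arm and 102 in total. That is a separate matter and does not bear on direction.

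**Step 2: the rule applied to the article's figures.** The rule is met in direction when the systemic mean exceeds the intratympanic mean.

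| Source | Intratympanic | Systemic | Arm that gained more | Rule, improvement coding | Rule, day 30 minus baseline |
|---|---|---|---|---|---|
| Sample size calculation | 30.7 | 28.7 | intratympanic | 28.7 > 30.7: not met | −28.7 > −30.7: met |
| Discussion, pilot | 40 | 30 | intratympanic | 30 > 40: not met | −30 > −40: met |
| Discussion, cited trial | 28.7 | 30.7 | systemic | 30.7 > 28.7: met | −30.7 > −28.7: not met |

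Under improvement coding the rule gives the wrong answer in all three rows. Under day 30 minus baseline it gives the right answer in all three. The first and third rows also show the same pair of figures attached to opposite arms.

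**Step 3: operating characteristics under improvement coding.** The standard error of the difference is 3 × √(2/48) = 0.612, so a true 2 dB difference lies 2/0.612 = 3.266 standard errors from 0.

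- Intended direction (intratympanic exceeds systemic), intratympanic 2 dB better: Φ(3.266 − 1.960) = Φ(1.306) = 90.4%.
- Direction as printed, intratympanic 2 dB better: 1 − Φ(1.960 + 3.266) = 1 − Φ(5.226) = 8.7 × 10⁻⁸.
- Direction as printed, intratympanic 2 dB worse: Φ(1.306) = 90.4%.

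With the t distribution in place of the normal, the figures are 89.8%, 1.0 × 10⁻⁷ and 89.8%. With 45 evaluable per arm (48 × 0.95 = 45.6, rounded down), the normal approximation gives 88.5%, 1.5 × 10⁻⁷ and 88.5%. These are the planned power with its direction turned round. Under day 30 minus baseline coding the printed direction is the intended one, and the power is the planned 90%.

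**The case against.** The strongest defence is that the rule is correct as printed. The Abstract and the Outcome measures section define change as running from the first audiogram to the 30-day audiogram, which reads naturally as follow-up minus baseline. Improvement is then negative, and the systemic mean exceeds the intratympanic mean exactly when intratympanic patients gained more. This stands as a possible reading. A reader might infer that the rule is simply backwards and that the trial will name the worse arm the winner. The documents do not support that, because they never fix the sign. Nor do they support the defence fully: the Statistical analysis section's own description of the difference is neutral, and no change figure in the article is negative.

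A second defence is that the intent is plain. The superiority hypothesis stands immediately before the rule, and the Discussion repeats the aim, so an analyst reading the whole article would probably not declare the arm with less improvement superior. That lowers the likelihood of a reversed conclusion. It does not remove the conflict, and a one-sided direction should not be left to inference once data exist.

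Third, the planning values are a weak anchor, because their arm labels conflict with the Discussion. This is right. The case for a positive scale therefore rests mainly on the Discussion, where both sets of figures are called improvement.

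A reader might also infer that the rule is a bare comparison of means with no confidence limit. That does not hold: the same paragraph specifies the t test and the 95% confidence interval method.

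**Conclusion.** The point holds as a conflict over the direction of the one-sided primary test. The sign of change is undefined. On the scale of every change figure in the article the rule is reversed, and it is right only under a coding that the endpoint wording permits but no figure uses. This is a contradiction in printed text, so it cannot be treated as detail left to a fuller document.

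The size is conditional. The probabilities of about 90% (when intratympanic is 2 dB worse) and about 10⁻⁷ (when it is 2 dB better) assume improvement coding, literal use of the printed direction, the one-sided 2.5% test, an SD of 3 dB and 48 per arm. Under the other coding there is no error. Because the fix is so small and the endpoint is primary, it should be made before allocation is revealed.

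**What to change.** Replace the superiority sentence with wording such as: Improvement is baseline PTA minus 30-day PTA, so positive values mean better hearing. Intratympanic treatment is superior if the lower limit of the two-sided 95% confidence interval for the difference in mean improvement (intratympanic minus intravenous) is above 0. This matches the one-sided 2.5% error already stated. Use the same definition in the Abstract, Outcome measures and Sample size calculation.

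Reconcile the arm labels for 30.7 and 28.7 between Sample size calculation and Discussion. If the Discussion's labels are the correct ones, those figures do not support a 2 dB advantage for intratympanic treatment, and the source of the planning difference must be restated.

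The cost is one sentence and a check of labels against the source, with no new data. Fixing the direction does not alter the sample size.

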#### Inclusion criteria

Patients will be enrolled if they have a clinical diagnosis of SSNHL with diabetes mellitus. SSNHL is defined as a sensory neural hearing loss greater than 30 dB across three contiguous pure-tone frequencies of pure tone audiometry occurring within 72 h. A diagnosis of diabetes mellitus will be based on the Standards of Medical Care in Diabetes-2010 [13]. Pure-tone average (PTA) will be calculated using the arithmetic mean of the hearing thresholds at 500, 1000, 2000, and 4000 Hz in the affected ear. Patients must have unilateral SSNHL. Study participants mus be between 18 and 65 years old. The time from onset to admission must be within 30 days and the hearing loss must have been deemed idiopathic following a suitable otolaryngologic evaluation. This will include medical and otologic history and extensive systems review, head and neck otologic and neurotologic physical examination, audiometry, and imaging to rule out structural or retrocochlear conditions, such as vestibular schwannoma, stroke, or demyelinating disease.

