### Randomization and blinding

Study participants will be randomly allocated to one of two different treatment groups at a 1:1 ratio using the SAS9.2 software with block randomization; block = 4 or 6. Randomization will be concealed until interventions are assigned and enrollment, follow up, data collection, data cleaning, and analysis are performed. It will not be possible to blind the study participants, physicians and paramedics. The investigators, outcomes assessors, and statisticians will be blinded to treatment allocation, and the allocation will only be revealed at the end of study. The randomization list and blinding codes will be kept strictly confidential.

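### The primary analysis is a valid but unadjusted t test on change in PTA; adjusting for baseline PTA would usually be more precise and needs no new data

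*Protocol article*

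**What the plan says.** All references are to the protocol article.

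- **Endpoint (Outcome measures):** "The primary outcome measure will be the change in PTA (dB) from the first audiogram to the 30-day follow-up audiogram".
- **Analysis (Statistical analysis):** "The primary outcome, i.e., change in PTA, will be calculated as the difference between the baseline and 30-day follow-up visit". The section continues: "This will then be compared between the two groups using a one-sided *t* test". The decision rule is "The two groups will be compared using the 95% confidence interval method to determine superiority".
- **Sample size (Sample size calculation):** the trial is sized on the same test, at one-sided 2.5% and 90% power, with a mean difference of 2 dB and an SD of 3 dB. The stated total is 96, said to allow for 5% loss.
- **Randomization (Randomization and blinding):** 1:1 by "block randomization; block = 4 or 6". No stratification factor is named.
- **Eligibility (Inclusion criteria):** hearing loss above 30 dB with no upper limit, and "The time from onset to admission must be within 30 days".

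No section names a covariate, an adjusted model or an adjusted sensitivity analysis. The protocol itself fixes the test, so the choice has not been left to an unseen analysis plan.

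**The concern.** How much a patient can gain is bounded by the starting threshold, so change in PTA can be expected to depend on baseline PTA. Patients may enter with any loss above 30 dB and up to 30 days after onset, and nothing in the randomization balances either factor.

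Subtracting the baseline amounts to adjusting for it with a slope fixed at 1. If the true slope is something else, part of the baseline variation stays in the outcome as noise. ANCOVA estimates the slope from the data and removes that part. Baseline PTA is needed to compute the endpoint, so it is already collected.

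Power is what is at stake, and the design has none to spare. The working shows that 96 is the requirement before the stated loss is taken off.

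**Working it through.** **Inputs from the protocol article.** Difference 2 dB, SD of change 3 dB, one-sided alpha 2.5%, power 90%, 5% loss, 48 per arm.

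**Inputs not in the documents (assumptions).** rho, the correlation between baseline and 30-day PTA; and k = SD at 30 days / SD at baseline. Both are varied below, with the SD of change held at 3 dB.

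**Step 1: the plan's own figure.**

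n per arm = 2 × (1.960 + 1.282)² × 3² / 2² = 47.3, rounded up to 48, or 96 in total.

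This reproduces 96, but before any loss. Allowing for 5% loss gives 48 / 0.95 = 50.5, so 51 per arm and 102 in total. With 96 randomized and 5% lost, 48 × 0.95 = 45.6 per arm remain. The planned t test then has 88.3% power (noncentral t; 88.9% by the normal approximation).

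**Step 2: precision of the two analyses.** With baseline SD s:

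- Variance of change = s²(1 + k² − 2·rho·k)
- Residual variance after adjusting for baseline = s²k²(1 − rho²)
- Slope of 30-day on baseline PTA: b = rho × k
- Ratio (ANCOVA / change score) = k²(1 − rho²) / (1 + k² − 2·rho·k) = 1 − (1 − b)² / (1 + k² − 2·rho·k)

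The second form of the ratio shows that the gain depends on how far b is from 1. It does not depend on rho alone. For k = 1 the ratio reduces to (1 + rho)/2.

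**Step 3: power with equal SDs (k = 1).** The SD of change is multiplied by the square root of the ratio; 45.6 per arm; noncentral t.

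| rho | variance ratio | reduction | power |
|---|---|---|---|
| t test on change | 1.00 | – | 88.3% |
| 0.9 | 0.95 | 5% | 89.8% |
| 0.7 | 0.85 | 15% | 92.7% |
| 0.5 | 0.75 | 25% | 95.3% |
| 0.3 | 0.65 | 35% | 97.4% |

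**Step 4: cases where the gain is small or nil.**

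| k | rho | slope b | variance ratio |
|---|---|---|---|
| 1.5 | 0.5 | 0.75 | 0.96 |
| 1.3 | 0.7 | 0.91 | 0.99 |
| 1.25 | 0.8 | 1.00 | 1.00 |

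**Step 5: simulation (45 per arm, 5,000 runs per scenario).** Power for the t test versus ANCOVA with k = 1 was 0.877 vs 0.975 (rho 0.3), 0.881 vs 0.951 (0.5), 0.882 vs 0.924 (0.7) and 0.872 vs 0.886 (0.9). With slope 1 (k = 1.25, rho 0.8) it was 0.868 vs 0.863. One-sided type I error was near 2.5% for both methods in every scenario.

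**Step 6: price of the covariates.** At about 91 evaluable patients, the variance inflation is 88/87 = 1.011 for one covariate and 88/86 = 1.023 for two.

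**The case against.** The strongest reply is that nothing here is wrong. Under 1:1 randomization the t test on change is unbiased and holds its type I error, it was fixed in advance, and it is the test on which the trial was sized. The size of the gain rests on two quantities the documents do not give. If some patients recover and others do not, the 30-day spread may exceed the baseline spread, which can bring the slope near 1 and the gain near zero. All of this stands. It makes the point one of efficiency and robustness, and it means the result must be given as a range.

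A reader might infer stronger claims that the documents do not support:

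- **That a change score over-corrects whenever rho is below 1.** It does so only when rho × k is below 1. With k = 1.25 and rho = 0.8 there is no over-correction.
- **That chance baseline imbalance biases the result, or is a second harm on top of lost power.** The t test's standard error already includes it, so it is the same loss of precision described another way.
- **That an ordinary imbalance could equal the whole 2 dB target.** Assume a baseline SD of 20 dB, equal SDs and rho 0.5. The standard error of the baseline difference is then 20 × √(2/48) = 4.08 dB, and a one-standard-error imbalance shifts the change-score difference by 0.5 × 4.08 = 2.0 dB. But the 2 dB target was planned with an SD of change of 3 dB. On that scale, with the same rho and equal SDs, the baseline SD is also 3 dB, the standard error is 0.61 dB and the shift is about 0.3 dB.
- **That the change is free.** The test is written into the protocol, and recruitment began on 1 March 2018, so an amendment is needed.

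**Conclusion.** The point holds as a weakness of efficiency and robustness. The planned test is valid, but it imposes a slope of 1 that nothing in the documents supports, and it leaves unused a covariate that is always collected.

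With equal SDs the variance falls by 35% to 5% for rho from 0.3 to 0.9, and power on the protocol's inputs rises from about 88% to between about 97% and 90%. With a larger SD at 30 days the gain can be 4% or less, and it is nil at slope 1. In that worst case the loss is the 1% to 2% of variance spent on degrees of freedom. The percentage reductions depend on rho and k. The power figures also depend on the protocol's 2 dB and 3 dB, which are taken here as given.

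Adjustment does not repair the shortfall between 96 and the 102 needed once the stated loss is included. That is a separate matter.

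**What to change.** By documented protocol amendment, before unblinding:

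1. Make the primary analysis a linear model of 30-day PTA on treatment and baseline PTA. Using change in PTA as the outcome in the same model gives the same treatment estimate apart from its sign, so the amendment should state which sign favours the intratympanic arm.
2. Judge superiority by the two-sided 95% confidence interval of the treatment coefficient. This keeps the one-sided 2.5% level of the sample size calculation.
3. Keep the unadjusted t test on change as a sensitivity analysis.
4. Optionally add time from onset to admission as a second pre-specified covariate. It has to be known to apply the eligibility limit, but the documents do not list it as an analysis variable, and its gain cannot be quantified from them.

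The Discussion already reports pilot results by arm, so the amendment should record what outcome data had been seen when the change was made.

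The cost is the amendment and 1 to 2 degrees of freedom. No new data are needed.

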## Method/design

### Design and setting

This study will be a randomized controlled trial that will be performed at the Peking University Shenzhen Hospital in China. We will enroll 86 patients with diabetes mellitus and SSNHL over a 3-year period. Study participants will be randomized at a ratio of 1:1 to receive either intratympanic methylprednisolone or intravenous methylprednisolone (Fig. 1). The study protocol will follow the Standard protocol items: recommendation for interventional trials (SPIRIT) recommendations for interventional trials (Additional file 1).

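### The primary t test uses only the baseline and day-30 audiograms; a baseline-adjusted repeated-measures model on audiograms already scheduled would fit the intention-to-treat statement better, at a small gain

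*Protocol article*

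**What the plan says.** All references are to the protocol article.

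- **Statistical analysis.** The primary outcome, change in PTA, "will be calculated as the difference between the baseline and 30-day follow-up visit". On the test: "This will then be compared between the two groups using a one-sided" t test, with the 95% confidence interval used to judge superiority. No covariate is named. On the analysis principle: "The analysis will be based on the thematic intention-to-treat principles".
- **Outcome measures.** Audiometry is scheduled "after 1 and 14 days of treatment, and at 30 and 90 days of follow up". PTA at 90 days is a secondary outcome; the article gives the day-1 and day-14 values no role in the primary comparison.
- **Sample size calculation.** "The difference in the mean was 2, and the combined standard deviation was 3"; "The type 1 error was 2.5% and statistical power was 90"%. On attrition: "Considering a 5% loss rate, 96 samples are required".
- **Data management and quality control.** Patients who wish to leave are asked whether they will still complete the scheduled evaluations, and losses and withdrawals are recorded and reported.
- **Randomization and blinding.** Participants, physicians and paramedics cannot be blinded.

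**The concern.** The article fixes both the variable and the test. The variable needs two audiograms, baseline and day 30. A patient who lacks the second has no observed value of it, and an ordinary two-sample t test has nothing to enter for that patient. Some loss is expected, and the article does not connect that loss to the intention-to-treat statement.

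Two things are at stake. The first is precision: information from the day-14 and day-90 audiograms, and from baseline PTA as a covariate, is collected but left out of the primary comparison. The second is bias: patients know their treatment, and one arm has repeated middle-ear injections while the other has infusions, so the reasons for missing day 30 could differ by arm. The planning difference is only 2 dB, so even a small arm-related shift deserves some protection.

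**Working it through.** **Inputs from the article.** Difference 2 dB, SD 3 dB, one-sided type I error 0.025, power 0.90, 5% loss, 1:1 allocation, 96 randomised (48 per arm).

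**Step 1: the plan's own figure.** Normal approximation: n per arm = 2 × SD² × (z0.975 + z0.90)² / difference² = 2 × 9 × (1.960 + 1.282)² / 4 = 47.3, rounded up to 48, or 96 in total. This is the figure before any loss. With 5% loss it would be 48 / 0.95 = 50.5, rounded up to 51 per arm, or 102. The stated 96 therefore has no room for the loss it mentions. That is a separate matter, but it means that any loss takes power below the target.

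**Step 2: power if only patients with a day-30 value are analysed.** At 5% loss, 48 × 0.95 = 45.6 per arm, about 91 patients in total.

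| Analysed per arm | Power, exact t | Power, normal approximation |
|---|---|---|
| 48 (nobody missing) | 0.898 | 0.904 |
| 45.6 (5% missing) | 0.883 | 0.889 |

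The loss is about 1.5 percentage points.

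**Step 3: what keeping patients in could recover.** Suppose that each patient without day 30 contributes a share ρ² of a full observation through other visits, where ρ is the correlation between those values and the day-30 value. The article gives no ρ; take 0.5 to 0.9 as an assumed range. Effective n per arm = 48 × (1 − 0.05 × (1 − ρ²)).

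- ρ = 0.5: 48 × (1 − 0.05 × 0.75) = 46.2, exact-t power 0.887.
- ρ = 0.9: 48 × (1 − 0.05 × 0.19) = 47.5, exact-t power 0.896.

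Against 0.883, the gain is about 0.4 to 1.3 points. Baseline adjustment may add more, but the article does not give the correlation needed to quantify it.

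**Step 4: possible bias.** Suppose that 5% of one arm (0.05 × 48 = 2.4 patients) have no day-30 value, that their mean change differs from that of the observed patients by a gap g, and that the other arm is complete. The shift in the estimated difference is 0.05 × g. Gaps of 1 and 2 of the protocol's SDs are used, as an assumption.

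| Gap g | Shift | Share of 2 dB | Remaining difference if the shift opposes the effect | Power, exact t (46 v 48 analysed) |
|---|---|---|---|---|
| 0 | 0 | 0% | 2.00 dB | 0.89 |
| 3 dB | 0.15 dB | 7.5% | 1.85 dB | 0.84 |
| 6 dB | 0.30 dB | 15% | 1.70 dB | 0.78 |

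If the shift ran the other way, it would flatter the intratympanic arm by the same amount. If both arms lost the same share with the same gap, it would cancel.

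**Step 5: who can be kept in.** A patient with a day-14 audiogram but no day 30 can be kept, and so can one who misses day 30 and returns at day 90. A patient who leaves before day 14 and never returns has at most the baseline and day-1 audiograms, and a model on days 14, 30 and 90 cannot use them.

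**The case against.** A reader might infer that the t test drops every patient without a day-30 audiogram and so breaks intention to treat. The article does not support that. It states no exclusion rule, and the same t test could be run after multiple imputation with every randomised patient kept. Intention to treat first means analysis in the arm assigned, and a missing outcome does not by itself contradict it. The request that withdrawing patients complete the scheduled evaluations points towards keeping outcome data. The full protocol and analysis plan are not shown, and a missing-data rule is commonly placed there, so its absence from the article is no finding. All of this stands.

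A reader might also be tempted to assume much larger gaps between missing and observed patients, say 10 to 30 dB, and report a collapse in power. Those gaps are 3.3 to 10 times the protocol's SD of 3 dB. If the SD is right, they are not credible; if they are credible, the SD is wrong and power computed from it means nothing. They cannot be used.

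Finally, it can be said that preferring a mixed model at 5% expected loss is a matter of taste, that the model assumes data missing at random, and that it too leaves out some early leavers. The last two points are correct and limit the benefit. The first is only partly so: the article does fix the primary estimator, that estimator uses two of the scheduled audiograms and no baseline covariate, and a method that makes better use of the same data is available at little cost.

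**Conclusion.** The point holds as an improvement to a stated method. As written, the primary t test gives a patient without a day-30 value no place, sits loosely beside the intention-to-treat statement, and leaves scheduled audiograms unused. It is not shown that patients will be excluded or that intention to treat is violated.

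The benefit of changing is small at the planned loss: about 1 point of power from retained patients, plus an unquantified gain from baseline adjustment, and some protection against a shift of the order of 0.15 to 0.3 dB. These sizes rest on the protocol's SD of 3 dB, 5% loss, an assumed ρ of 0.5 to 0.9, and an assumed gap of 3 to 6 dB confined to one arm. They would grow with higher loss: exact-t complete-case power at 96 randomised is about 0.865 at 10% and 0.82 at 20%. The model's protection holds only if the data are missing at random given baseline and the observed visits.

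**What to change.** Replace the primary t test by a mixed model for repeated measures on PTA at days 14, 30 and 90.

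- Terms: baseline PTA, treatment, visit and treatment-by-visit, with an unstructured covariance across visits.
- Patients analysed in the arm to which they were randomised, including every patient with at least one of these audiograms. State the number who have none, by arm.
- Primary result: the day-30 treatment contrast with its two-sided 95% confidence interval, which matches the one-sided 2.5% level in the sample size section. With baseline in the model, the contrast in day-30 PTA and the contrast in change to day 30 are the same quantity apart from sign, so the primary outcome does not change. State the sign convention.
- One delta-adjusted sensitivity analysis, in which the missing day-30 values in one arm are made progressively worse, to show how far the missing-at-random assumption can fail before the conclusion changes.

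The cost is analysis wording and modest programming in SAS, which the article already names. No new visits or data are needed. The change should be dated and made before allocation is revealed to the statisticians.
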